# Protocol for a multi-site randomised controlled feasibility study investigating intermittently scanned blood continuous glucose monitoring use for gestational diabetes: the RECOGNISE study

**DOI:** 10.1186/s40814-023-01341-y

**Published:** 2023-07-11

**Keywords:** Gestational diabetes, Continuous glucose monitoring, Feasibility study, Large for gestational age

## Abstract

**Background:**

Incidence of gestational diabetes mellitus (GDM) is increasing and is associated with adverse perinatal outcomes including macrosomia, pre-eclampsia, and pre-term delivery. Optimum glycaemic control can reduce these adverse perinatal outcomes. Continuous glucose monitoring (CGM) informs users about interstitial glucose levels allowing early detection of glycaemic excursions and pharmacological or behavioural intervention. Few adequately powered RCTs to evaluate the impact of using CGM in women with GDM on perinatal outcomes have been undertaken.

We aim to establish the feasibility of a multi-site RCT to evaluate the clinical- and cost-effectiveness of an intermittently scanned continuous glucose monitor (isCGM) compared with self-monitored blood glucose (SMBG) in women with GDM for reducing fetal macrosomia and improving maternal and fetal outcomes. We will evaluate recruitment and retention rates, adherence to device requirements, adequacy of data capture and acceptability of trial design and isCGM devices.

**Methods:**

Open-label multicentre randomised controlled feasibility trial. Inclusion criteria: pregnant women, singleton pregnancy, recent diagnosis of GDM (within 14 days of commencing medication, up to 34 weeks gestation) prescribed metformin and/or insulin. Women will be consecutively recruited and randomised to isCGM (FreestyleLibre2) or SMBG. At every antenatal visit, glucose measurements will be evaluated. The SMBG group will use blinded isCGM for 14 days at baseline (~ 12–32 weeks) and ~ 34–36 weeks. The primary outcome is the recruitment rate and absolute number of women participating. Clinical assessments of maternal and fetal/infant health will be undertaken at baseline, birth, up to ~ 13 weeks post-natal. Psychological, behavioural and health economic measures will be assessed at baseline and ~ 34–36 weeks gestation. Qualitative interviews will be undertaken with study decliners, participants, and professionals to explore trial acceptability, of using isCGM and SMBG.

**Discussion:**

GDM can be associated with adverse pregnancy outcomes. isCGM could offer a timely, easy-to-engage-with intervention, to improve glycaemic control, potentially reducing adverse pregnancy, birth and long-term health outcomes for mother and child. This study will determine the feasibility of conducting a large-scale multisite RCT of isCGM in women with GDM.

**Trial registration:**

This study has been registered with the ISRCTN (reference: ISRCTN42125256, Date registered: 07/11/2022).

**Supplementary Information:**

The online version contains supplementary material available at 10.1186/s40814-023-01341-y.

## Background

Gestational diabetes mellitus (GDM) is glucose intolerance with onset during pregnancy, typically resolving after birth [1, 2] GDM affects 5–10% of UK (United Kingdom) pregnancies (35,000–70,000 women yearly) [2, 3]. Incidence estimates vary due to different screening methods, but is increasing rapidly due to higher rates of obesity and pregnancies in older women [4, 5].

Women diagnosed with GDM are primarily advised about lifestyle changes. If these are ineffective in controlling blood glucose, they are offered medications such as metformin and/or insulin, depending on local or national guidance [3]. Recommended current standard care for women with GDM in the UK is self-monitoring of capillary blood glucose (SMBG) four to seven times daily using ‘finger-prick’ testing [3]. Barriers to SMBG include stigma of public testing, anxiety, pain and inconvenience [6]. Moreover, the glucose variability and transient glucose excursions from target blood glucose ranges that may be experienced during pregnancy are not easily detectable using SMBG [6, 7].

High levels of glycaemia in women with GDM are associated with risk of adverse pregnancy and birth outcomes for mother and baby. Recent studies [8–10] and a meta-analysis [11] have investigated the association between GDM and adverse pregnancy outcomes. In a meta-analysis of 156 studies of over 7 million pregnancies, where data was examined for women who did not use insulin, women with GDM compared with those without had increased risk of caesarean section, pre-term delivery, low 1 min Apgar score, fetal macrosomia, and large for gestational age (LGA) infant. In women with GDM who were prescribed insulin (in whom lifestyle changes may not have achieved target glucose levels) there was increased risk of having an LGA infant, an infant with respiratory distress syndrome, jaundice, or requiring neonatal intensive care (NICU) admission compared with women without GDM [11]. Improved glycaemic control can reduce these complications [11].

High overnight glucose levels in women with GDM are associated with fetal macrosomia, which go undetected by SMBG [12]. To address the shortcomings of SMBG, continuous glucose monitoring devices (CGMs) have been developed, which measure interstitial fluid glucose levels using a small subcutaneous sensor. These provide more frequent measurements and a more detailed picture of glucose levels over 24 h, identifying glucose fluctuations. They can immediately alert women to excursions (hypo/hyperglycaemia) using alarms [13]. The intermittently scanned Continuous Glucose Monitor-isCGM (or “Flash” device) provides continuous glucose data if the patient swipes their arm sensor at least every 8 h with a smartphone/reader. CGM data enable better clinical decision-making about medication and behavioural modifications, (diet, physical activity, glucose monitoring, and medication adherence) to help control glucose levels. The healthcare team can also remotely monitor women, reducing burden on services and users. CGM could also provide better oversight in those who do not reach advised glucose targets and potentially in those who do not speak the same language as healthcare providers.

Systematic review data indicates that CGM devices improve clinical outcomes in non-pregnant adults with diabetes, reducing HbA1C and time in hypo/hyperglycemia [14, 15]. In pregnant women with type 1 diabetes mellitus, the CONCEPTT trial demonstrated less glycaemic variability, reduction in fetal macrosomia and NICU admissions in those using CGM devices compared with SMBG [16]. The use of CGM devices has become commonplace outside pregnancy, and is recommended by NICE for pregnant women with type 1 diabetes mellitus [17]. However, systematic reviews indicate that little research has investigated CGM use in women with GDM; a Cochrane review identified two low-quality RCTs comparing CGM and SMBG in women with GDM, and found no difference in outcomes for mother or baby, including caesarean rate, fetal macrosomia, neonatal hypoglycaemia, and perinatal death [18]. The most recent systematic review and meta-analysis of six RCTs investigating the effect of CGM compared with SMBG identified that CGM use in GDM was associated with reduced HbA1c levels, lower gestational weight gain, and lower birth weight, but no other outcomes measured including mean fasting or postprandial blood glucose, hypertensive disorders, fetal macrosomia/LGA, or neonatal hypoglycaemia [19].

Together, these data indicate limited high-quality evidence examining the use of CGM devices in women with GDM in pregnancy. The studies described all have major limitations: extremely small sample sizes, limiting their statistical power to detect changes in clinical outcomes; short-term device usage rather than throughout pregnancy; use of less accurate, now outdated, devices that did not always provide real-time data, and sub-optimal adherence to device requirements [18, 20, 21]. No RCT has targeted women who are prescribed metformin or insulin who have not reached glycaemic targets with lifestyle interventions, and in whom the most benefit is likely to be achieved. It will result in having additional data to inform care if they have not adhered to regular SMBG and a clearer picture for clinicians of where within the 24-h window problems may lie, to advise lifestyle and medication changes. Furthermore, no studies report investigating the acceptability of the intervention, particularly in relation to different sociodemographic groups or underserved women, in whom increased risk of adverse pregnancy outcomes has been identified [22].

To date, no RCT has been conducted to establish the effectiveness, safety and cost-effectiveness of isCGM devices in women with GDM, despite the potential substantial health improvement for both mother and baby. Feasibility work is needed to determine whether a high-quality multi-site RCT can be conducted, to assess whether women will agree to participate in an RCT, acceptability of randomisation and data collection processes, and whether adequate data capture can be achieved to inform efficacy and health economic analyses. In addition, it is important to understand adherence to the device requirements and acceptability of isCGM and using masked devices within a control arm.

The RECOGNISE (taRgeted intermittEnt gluCose mOnitoring for the management of GestatioNal dIabeteS mEllitus) study aims to establish the feasibility of an RCT to evaluate the clinical- and cost-effectiveness of CGM devices (an intermittently scanned-isCGM device), compared with SMBG, for reducing fetal macrosomia, and improving pregnancy and health outcomes in women diagnosed with GDM who have been prescribed medication for management.

Research questions:Will women agree to participate in an RCT comparing isCGM and SMBG, and is randomisation acceptable?Do women adhere to the requirements of the isCGM device?Can we collect the data necessary to understand clinical effectiveness, experience and health economic outcomes (completeness of self-report data, glycaemic control monitoring data, and extraction from medical records)?Is isCGM acceptable to women with GDM? Does this vary by socio-demographic factors?Is isCGM acceptable to healthcare professionals who care for women with GDM?Do women and healthcare professionals find glucose readings from isCGM devices useful to inform treatment modification and management, and to optimise glycaemic control?

## Method

This protocol adheres to the SPIRIT framework for reporting of study protocols [23]. Figure 1 describes the study flow and Fig. 2 provides the SPIRIT figure.

**Fig. 1 Fig1:**
[figure not shown]
Study flow diagram

**Fig. 2 Fig2:**
[figure not shown]
SPIRIT figure

### Study design and setting

This study is designed as a multi-centre, open, randomised controlled feasibility study with embedded qualitative research, conducted in two UK maternity units: North Bristol NHS Trust (NBT) and Somerset NHS Foundation Trust (SFT). The feasibility study is sponsored by North Bristol Trust.

### Participants

Women who have diagnosed GDM in their current pregnancy according to NICE criteria (2-h 75 g oral glucost tolerance test [OGTT]), who have not established target glycaemic control using lifestyle modification alone will be recruited up to 34 + 0 weeks of pregnancy. Table 1 indicates inclusion and exclusion criteria for the study. We will use the National Institute for Health and Care Research (NIHR) INCLUDE Framework to achieve representation of underserved (including black and minority ethnicity) women [24].

**Table 1 Tab1:** Inclusion and exclusion criteria

Inclusion	Exclusion
• Aged 16–55 • GDM diagnosed at any gestation (typically > 12 weeks) per NICE guidelines: oral glucose tolerance test demonstrating a fasting plasma glucose level of 5.6 mmol/litre or above or a 2-h plasma glucose level of 7.8 mmol/l or above [3] • Has commenced medication (metformin ≥ 500 mg/day) and/or insulin) within the previous 14 days • ≤ 34 + 0 weeks of gestation • Primiparous or multiparous • Singleton pregnancy • Not met NICE glucose targets with lifestyle modification of fasting glucose below 5.3 mmol/l, 1 h after meals below 7.8 mmol/l OR 2 h after meals below 6.4 mmol/l [3] • Able to give informed consent to participate	• Aged < 16 or > 55 • Not prescribed insulin or at least 500 mg/day metformin, OR commenced medication > 14 days ago • Met NICE glucose targets with lifestyle modification • > 34 + 0 weeks gestation • Chronic kidney disease • Psychiatric inpatient treatment, • History of bariatric surgery or other surgeries that induce malabsorption • Long-term use (> 2 weeks) of systemic steroids within 2 weeks prior to enrolment • Multiple pregnancy • Unable to give informed consent to participate

### Screening and consent

Women will be informed of the study by their healthcare professional (HCP); obstetrician, endocrinologist, diabetes specialist nurse, or specialist midwife in their first specialist diabetes antenatal clinic appointment where they are referred after diagnosis of GDM. Interested patients will be given a Participant Information Leaflet (PIL). PILs will be translated into four languages, targeting the groups of women who do not speak English as a first language most frequently seen in our GDM clinics: Arabic, Bangladeshi, Polish, and Romanian. All women will also have access to a recruitment video (with preferred language voiceover/subtitles). Patients will be followed up with a telephone call by a Research Practitioner to discuss the study prior to their next appointment, with verbal translation used as needed. At their next specialist diabetes antenatal clinic appointment, the clinician will identify women meeting the above inclusion criteria—those who have not met the glucose control targets and therefore are prescribed metformin (≥ 500 mg/day) and/or insulin. They will be invited to participate, have an opportunity to ask questions and have written informed consent obtained by a Research Practitioner.

### Sample size

#### Quantitative sample size

There are approximately 6000 and 3000 births/year at NBT and SFT, respectively. At NBT 440 patients are diagnosed with GDM each year (180 and 90 women per year on insulin or at least 500 mg/day of metformin will be seen in clinics after exclusions, in NBT and SFT respectively). With a 60% participation rate of those eligible women, we could recruit 108 per year at NBT and 54 per year at SFT. A 12-month recruitment period at both sites will be sufficient to meet our target, allowing for unforeseen recruitment delays. We will be able to estimate a participation rate of 60% to within 95% confidence interval of 52% to 68%.

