#### Qualitative sample size

The qualitative sample size estimation is pragmatic, accounting for study sample size (*n* = 60) and information power [25], whereby sample size is determined by the research aims (narrow/broad), theoretical underpinnings (whether theory informs the topic guide), and dialogue quality (researcher topic-related knowledge), and within versus cross-case analysis. An experienced researcher with diabetes-specific knowledge will carry out this work, which has focused aims. Behavioural science frameworks will inform the topic guides and a cross-case analyses will be conducted. Recruitment of up to 20 intervention group (12–14 NBT; 6–8 SFT), and 10 control group participants (6–7 NBT; 3–4 SFT) represents approximately 50% of study participants, balancing proportion of expected recruitment at each site. A further 6–8 women declining participation (4–5 NBT, 2–3 SFT), and up to 10 healthcare professionals (HCPs) across sites (6–7 NBT, 3–4 SFT) is considered an appropriate sample size to answer the questions addressed.

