### Outcomes

The primary outcome for this feasibility study is the recruitment rate and the absolute number of women participating in the study. Recruitment outcomes will include: number of women invited to study, number of women meeting eligibility criteria, number of women recruited, and follow-up and dropout rates (attrition). Reasons for declining participation will be explored in the embedded qualitative study.

Adverse events are defined as any untoward medical occurrence in a randomised patient regardless of its causal relationship to study treatment. Provision has been made for actively recording adverse events, which are expected, for example, pain or bleeding during the device application. All adverse events that occur during the study period will be documented on a designated data form. Adverse events will be recorded and reported in accordance with the Sponsor’s Safety Reporting SOP.

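### The 95% confidence interval stated for participation (52% to 68%) is narrower than a 60-woman study gives; at 60% participation it would be about 50% to 70%

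*Protocol article*

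**What the plan says.** The Outcomes section defines the primary outcome: "The primary outcome for this feasibility study is the recruitment rate and the absolute number of women participating in the study".

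The Quantitative sample size section of the protocol article gives the supply of eligible women: "180 and 90 women per year on insulin or at least 500 mg/day of metformin will be seen in clinics after exclusions", at NBT and SFT respectively. It then applies the assumed rate: "With a 60% participation rate of those eligible women, we could recruit 108 per year at NBT and 54 per year at SFT". On duration it says: "A 12-month recruitment period at both sites will be sufficient to meet our target, allowing for unforeseen recruitment delays". It closes with the precision claim: "We will be able to estimate a participation rate of 60% to within 95% confidence interval of 52% to 68" per cent. The section does not say what the target is or how many eligible women the interval is based on.

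The study size appears only in the next section, Qualitative sample size, which describes the interview numbers as "accounting for study sample size (*n* = 60) and information power". That section plans up to 20 intervention and 10 control interviewees, and says this "represents approximately 50% of study participants, balancing proportion of expected recruitment at each site".

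**The concern.** The precision of an estimated participation rate depends on how many eligible women are counted in its denominator. The article leaves that number to be worked out, and the one study size it gives leads to a wider interval than the one printed. The interval is the only precision argument offered for the size of the study, and it concerns part of the primary outcome. A reader planning the definitive trial would take the rate to be known to within 8 points, when a study of 60 women gives somewhat less than that.

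**Working it through.** **Inputs**
- Assumed participation: p = 0.60 of eligible women (Quantitative sample size).
- Stated 95% interval: 52% to 68%, a half-width of 8 points (same section).
- Eligible women per year: 180 + 90 = 270 (same section). The yearly recruits confirm that this is the base of the rate: 0.60 × 180 = 108 and 0.60 × 90 = 54, together 162.
- Women recruited: 60 (Qualitative sample size). Cross-check: 20 + 10 = 30 interviewees, described as about half of participants, gives 30 / 0.5 = 60.

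**Denominator implied by the stated size**

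Eligible women = 60 / 0.60 = 100.

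**Attempt to reproduce the stated interval**

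Wald: p ± 1.96 × √(p(1 − p)/n) = 0.60 ± 1.96 × √(0.24/100) = 0.60 ± 0.096, or 50.4% to 69.6%.

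Other 95% methods with 60 of 100:

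| Method | 95% interval |
|---|---|
| Wilson | 50.2% to 69.1% |
| Exact (Clopper–Pearson) | 49.7% to 69.7% |
| Jeffreys | 50.2% to 69.2% |
| Wald with continuity correction | 49.9% to 70.1% |

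None rounds to 52% to 68%. The Wald half-width is 9.6 points against 8, a ratio of 1.20.

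**Number of eligible women that gives the stated interval**

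For a half-width of exactly 8 points: n = 1.96² × 0.24 / 0.08² = 144 eligible women, and 0.60 × 144 = 86 recruits.

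The article prints whole percentages, so a range of n is compatible with it:
- n = 128: 0.60 ± 0.085, or 51.5% to 68.5% (unrounded 51.51 and 68.49), with 0.60 × 128 = 77 recruits.
- n = 163: 0.60 ± 0.075, or 52.5% to 67.5% (unrounded 52.48 and 67.52), with 0.60 × 163 = 98 recruits.

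Both round to 52% to 68%. The Wald interval therefore reads as printed for 128 to 163 eligible women, and even the lower end implies more than 60 recruits.

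**Other routes to the printed figure**

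| Basis | Interval | Comment |
|---|---|---|
| n = 60, 95% | 47.6% to 72.4% | recruits used as denominator |
| n = 270, 95% | 54.2% to 65.8% | all eligible women in 12 months |
| n = 162, 95% | 52.5% to 67.5% | rounds to the printed figure, but 162 is the yearly number of recruits |
| n = 100, 90% | 51.9% to 68.1% | rounds to the printed figure, but the article says 95% |
| n = 100 of 270, 95%, finite-population correction | 52.4% to 67.6% | rounds to the printed figure; factor √(170/269) = 0.795; no correction is stated |

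Three of these routes give the printed interval. The first uses the wrong denominator for a participation rate, the second contradicts the stated confidence level, and the third needs an unstated correction that would limit the inference to these 270 women.

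**The case against.** The best defence is that the article never says the interval rests on 60 recruits. The figure of 60 stands in the section on interview numbers, and the 100 eligible women are a back-calculation. The interval may instead have been derived from expected throughput over 12 months: the 162 yearly recruits give 52.5% to 67.5%. It would therefore be wrong to infer that no number in the article yields the printed interval. This explains where the figure might have come from, but it does not justify it, because recruits are not the denominator of a participation rate. The link to 60 is an inference, but a firm one: 60 is called the study's sample size, and the interview percentage agrees with it.

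A second defence is that the success criteria table and the flow diagram are not shown, and either may state the target. For that reason little weight should be put on the target being absent from the quantitative section. The conflict remains in either case: a target of 60 would confirm it, and a target in the range of 77 to 98 would contradict the Qualitative sample size section.

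Three stronger readings are tempting, and the document does not support them.
- A reader might infer that the study needs exactly 144 eligible women and 86 recruits. That is one point within the rounding range of 128 to 163 eligible women.
- A reader might infer that the progression decision relies on overstated precision. The Success criteria section describes a traffic-light scheme that includes the recruitment rate, and the Statistical analysis section plans frequencies and percentages. No visible text uses the interval for progression.
- A reader might note that 60 of 270 is only 22%, and infer that the number could be met while the rate fails badly. That supposes all 270 women are approached over the full year and recruitment still stops at 60. The article presents 12 months as an allowance for delay, and the recruitment rate is part of the primary outcome alongside the absolute number.

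**Conclusion.** The point holds as a correction to the stated precision of part of the primary outcome, and it is of moderate weight. With 60 recruits at 60% participation, the 95% interval is about 50% to 70%. The half-width is 9.6 points, which is 1.6 points or 20% more than stated. The printed interval and the printed study size cannot both stand at the 95% level under any of the standard methods tried.

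This rests on three assumptions: that 60 is the number recruited, that the denominator is eligible women at the assumed 60%, and that no finite-population correction was intended. The document does not show that the study is too small for its feasibility aims, or that its conduct or safety is affected.

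**What to change.** In the Quantitative sample size section, state the target (60 recruited) and the denominator (about 100 eligible women at 60% participation). Name the interval method and give the precision as about 50% to 70%. This costs one or two sentences and a slightly less favourable figure; nothing in the design changes.

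If 52% to 68% was the intended precision, state the number of eligible women it rests on, and reconcile the Qualitative sample size section with it. The figure of 60 would change, and 30 interviewees would be about 31% to 39% of participants (30/98 to 30/77) rather than about half. At the article's own rate of 162 recruits a year, 77 to 98 recruits would take about 5.7 to 7.3 months (77/162 × 12 to 98/162 × 12), against 4.4 months for 60 (60/162 × 12). This option would therefore still fit the 12-month period, but it means a larger study rather than a wording change.
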